### Body image and femininity in breast cancer

1.3

The impact of mastectomy on body image represents a critical dimension of the psychological burden experienced by breast cancer patients (Türk et al., 2018). For many women, breasts symbolize femininity, sexuality, beauty, and motherhood, and their removal through mastectomy can result in profound disturbances to body image and self-concept (Fang et al., 2013; Koçan and Gürsoy, 2016). Research has documented that negative body image following mastectomy includes dissatisfaction with appearance, perceived loss of femininity and body integrity, reluctance to look at one’s body, feeling less sexually attractive, self-consciousness about appearance, and dissatisfaction with surgical scars (Koçan and Gürsoy, 2016; Latifee et al., 2025).

Studies have shown that mastectomy can be experienced as a sense of mutilation and diminished self-worth, threatening perceptions of femininity and potentially causing more psychological trauma than the cancer diagnosis itself (Fang et al., 2013; Türk et al., 2018). Body image distress is associated with additional complications including reduced quality of life, depression and anxiety symptoms, social isolation, and impairments in sexual functioning (Weingarden et al., 2022; Latifee et al., 2025). These psychological impacts may persist long after treatment completion, affecting social reintegration and intimate relationships, with some studies suggesting that adaptation may take up to 2 years following surgery (Izydorczyk et al., 2018).

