#### Sample size calculation

2.2.4

An *a priori* power analysis was conducted to calculate the minimum sample size required for this study, following established statistical procedures (Perugini et al., 2018; Taccini et al., 2022). The G*Power software (V.3.1.9.2) (Faul et al., 2007, 2009) was utilized to determine the required sample size for repeated measures analysis of variance (ANOVA) with within-between interaction. The research protocol involves four assessment timepoints, with treatment condition as between-group variable (TAU vs. TAU + psychoeducation vs. TAU+R-TEP) and time as within-subject variable (T0, T1, T2, and T3; see dedicated section).

Given the absence of prior studies implementing this specific intervention protocol, conservative a priori parameters were adopted. These were informed by examining previous studies utilizing similar interventions (though not identical), comparable target samples, and similar constructs. The effect size *f* was set to 0.15 (small-to-medium effect size) and the correlation among repeated measures was set to 0.35. Type I error rate probability (*α*) was set to 0.05 (two-sided), and power (1-*β*) was set at 0.80 (Cohen, 1988; Eid et al., 2017; Perugini et al., 2018).

G*Power analysis indicated 80% probability of correctly rejecting the null hypothesis of no significant group-by-time interaction effect with an overall sample of 102 participants (approximately 34 subjects per group). Based on average patient flow to the unit, to account for an anticipated attrition rate of approximately 20%, the study aims to recruit at least 122 patients, ensuring adequate statistical power for the planned analyses.

The three groups will each comprise a minimum of 34 patients: (A) Control group (G1): Patients receiving standard routine psychological support (TAU); (B) Active control group (G2): Patients receiving weekly psychoeducation session plus TAU; (C) Experimental group (G3): Patients receiving EMDR R-TEP intervention plus TAU.

This sample size is highly feasible considering service patient flow while simultaneously permitting statistical analyses generating reliable estimates.

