#### Randomization and blinding

2.2.5

The study employs a single-blind RCT design. Participant allocation to one of the three groups (TAU vs. TAU + psychoeducation vs. TAU+R-TEP) will follow rigorous procedures ensuring allocation concealment.

First, each participant will be assigned a unique identification code ensuring individual anonymity. Second, group allocation will be conducted through dedicated web-based software (Randomization.com) (Randomization, 2025) by two independent persons meeting the following requirements: (1) external to the project; (2) unaware of study objectives; (3) with no access to participant information; and (4) without mutual contact. If any condition is not met, these individuals will be replaced. This procedure ensures proper allocation concealment. Regarding blinding, participants are blinded to group assignment rationale, while treating clinicians are necessarily aware of intervention type given the nature of psychological treatments. Participants will be assigned to conditions within seven working days from baseline assessment.

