### Statistical analysis

2.6

Statistical data analyses will be performed using R software (R Core Team, 2017). Throughout data collection duration, *in itinere* statistical analyses will verify data quality and potential bias absence. Regarding missing data management, participants who discontinue the study (dropouts) will be excluded from analyses due to concerns about response validity. Similarly, assessment batteries with more than 10% missing items will be considered invalid and excluded. For remaining missing data within valid batteries, appropriate handling methods (e.g., multiple imputation, full information maximum likelihood) could be employed depending on missing data patterns and mechanisms.

Preliminary analyses will verify group homogeneity regarding relevant variables (age, comorbidity, social support, etc.) and possible intervening variable influence (covariates). If deemed appropriate and/or if significant heterogeneity is detected between groups, such variables will be included as covariates in the analysis models. Preliminary analyses will also verify psychometric instruments’ internal consistency (McDonald’s omega) (McDonald, 1999).

Both group-level aggregate analyses and individual change-focused evaluations will be employed. At group level, longitudinal changes will be examined using appropriate linear models for repeated measures data (e.g., linear mixed models or repeated measures ANOVA, or Bayesian approaches), depending on data characteristics such as distribution, missing data patterns, and sphericity assumptions (Howell, 2013; Darlington and Hayes, 2017; van den Bergh et al., 2023). Also, if appropriate, multilevel analysis – random slopes and/or random intercepts – may be implemented in the models (Hox et al., 2017; Heck and Thomas, 2020; Finch and Bolin, 2024). Model selection will be guided by standard diagnostic procedures. All models will test the interaction between time and intervention group – and where appropriate – controlling for individual variability and potential covariates identified in preliminary analyses.

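### Covariates may enter the outcome models through a significant baseline difference or because they are deemed appropriate; neither route uses a criterion fixed in advance

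*Protocol article*

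**What the plan says.** All of this is in the protocol article.

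- **Statistical analysis (2.6), the check.** "Preliminary analyses will verify group homogeneity regarding relevant variables (age, comorbidity, social support, etc.) and possible intervening variable influence (covariates"). Three variables are named and the list is left open.
- **Statistical analysis (2.6), the rule.** The sentence that turns the check into a model choice opens "If deemed appropriate and/or if significant heterogeneity is detected between groups". From its second condition to its end it reads "if significant heterogeneity is detected between groups, such variables will be included as covariates in the analysis models". There are therefore two routes: a significant baseline difference, or a judgement with no stated basis.
- **Statistical analysis (2.6), the link to the outcome.** Every model tests time by group and, where appropriate, does so while "controlling for individual variability and potential covariates identified in preliminary analyses".
- **Statistical analysis (2.6), single timepoints.** Optional between-group tests at each timepoint are described, with one-way ANOVA and Kruskal-Wallis as examples. Neither example adjusts for an earlier score.
- **Sample size calculation (2.2.4).** The number of patients was derived as the "required sample size for repeated measures analysis of variance (ANOVA) with within-between interaction", with T0, T1, T2 and T3 all as levels of the response.
- **Randomization and blinding (2.2.5) and Timeline and assessments (2.4.2).** Allocation is random and no stratification factor is named. The first section counts the time to assignment from the baseline assessment. The second places assignment after T1, which follows surgery.

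**The concern.** Among all randomised patients, a baseline difference between arms arises by chance. A significance test of that difference says nothing about whether the variable predicts distress or post-traumatic symptoms, which is what makes a covariate worth having. Used as an entry rule, the test admits irrelevant variables that happen to differ and passes over strong predictors whose difference is not significant.

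The second route does not repair this. A prognostic variable can enter through it, but only by a decision taken without a criterion after the arms have been compared. At stake are the precision of the primary comparison and the reader's assurance that the model was not chosen with the data in view. This is a rule that the article states, so it is not a detail left to a separate analysis plan.

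**Working it through.** **1. The plan's own sample size.** Inputs from Sample size calculation: k = 3 groups, m = 4 timepoints, f = 0.15, correlation 0.35, alpha 0.05. Sphericity (epsilon = 1) is my assumption.

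- Noncentrality = f² × N × m / (1 − 0.35) = 0.0225 × 102 × 4 / 0.65 = 14.12.
- Degrees of freedom: (3 − 1)(4 − 1) = 6 and (102 − 3)(4 − 1) = 297.
- Power at N = 102 is 0.807. The smallest N reaching 0.80 is 101, or 102 as a multiple of three.

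The stated 102 reproduces, so 34 per arm is used below.

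**2. How often the significance route acts.** I assume a 5% test for each variable, since the article gives no level for these checks. With c independent candidates, the chance that at least one is selected is 1 − 0.95^c.

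| Candidates | Chance that at least one enters |
|---|---|
| 3 | 14% |
| 5 | 23% |
| 8 | 34% |
| 10 | 40% |

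The article names three variables and leaves the list open, so the upper rows are assumptions.

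**3. What the route does to the test.** Simulation: 40,000 trials of 3 × 34 patients, one post-treatment comparison and one baseline covariate. The covariate-outcome correlation is assumed. For power, one arm is shifted by 0.65 SD, which gives about 78% to 79% unadjusted power.

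| Correlation | Covariate selected | Type I error, two-stage rule | Power, two-stage rule | Power, always adjusted |
|---|---|---|---|---|
| 0 | 5.2% | 4.9% | 79% | 78% |
| 0.35 | 5.0% | 4.7% | 78% | 83% |
| 0.5 | 5.1% | 4.3% | 79% | 89% |
| 0.7 | 5.1% | 3.9% | 80% | 97% |

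Selection does not depend on the correlation, so a covariate at 0.7 is left out about 95% of the time. Always adjusting keeps type I error at 4.9% to 5.1%. The two-stage rule errs low because it adjusts in exactly those trials where the unadjusted test rejects too often (29% of null trials with a significant imbalance, at correlation 0.7).

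**4. What the check leaves untouched.** At 34 per arm, a pairwise t-test is non-significant up to an observed difference of 2.00 × √(2/34) = 0.48 SD. The three-group F test is non-significant up to 0.60 SD between the extreme arms with the third midway: F = 34 × (d²/2)/2 = 8.5d², set equal to the critical value 3.09. With a covariate-outcome correlation of 0.35, such a difference shifts the unadjusted comparison by 0.35 × 0.48 = 0.17 SD to 0.35 × 0.60 = 0.21 SD, while the arms pass as homogeneous.

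**5. How a covariate can help the planned test.** The main test is time by group. If a time-constant covariate X enters with one coefficient g, each within-patient difference contains gX − gX = 0, so it adds no precision to that test. A gain requires a coefficient that varies with time, that is, a covariate-by-time term.

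**6. Single-timepoint comparisons.** At the planned correlation of 0.35, adjusting a T2 or T3 score for T0 leaves 1 − 0.35² = 0.8775 of the variance. Adjusting for T0 and T1 leaves 1 − 2(0.35²)/1.35 = 0.8185.

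**The case against.** The strongest reply is that the significance test is only one of two routes. The article also plans to examine the influence of covariates, so a balanced but prognostic variable can still be included. That is correct, and it would be wrong to say that chance imbalance alone decides the model. But influence on the outcome is never made the condition for entry, and the second route has no condition at all.

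Four stronger readings are tempting, and the article does not support them:

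- **That the model changes by luck about half the time.** This needs 12 to 20 tested variables (1 − 0.95^12 = 46%; 1 − 0.95^20 = 64%). That many baseline items can be counted if background data and questionnaire scores are included, but the article does not say that all are tested.
- **That the rule forfeits the precision held in the T0 and T1 scores.** Those scores are already response levels in the time-by-group model, so they are not dropped for being balanced. The 12% and 18% reductions in step 6 concern only the optional single-timepoint tests.
- **That the arms are compared unblinded.** The Limitations section says that independent researchers do the analysis. It does not say whether they know the arms.
- **That the article treats type of surgery as critical for the primary outcomes.** The sentence "The impact of mastectomy on body image represents a critical dimension of the psychological burden experienced by breast cancer patients" concerns body image, which is a secondary, exploratory outcome.

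One caveat also stands. Crossovers and dropouts are excluded from analysis, so some imbalance in the analysed set may be systematic. A significance test cannot separate that from chance.

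**Conclusion.** The point holds in limited form. The article fixes a covariate rule that is unrelated to prognostic value on one route and has no criterion on the other. The significance route admits each variable about 5% of the time, or at least one of 3 to 10 independent candidates 14% to 40% of the time; correlated candidates would lower these figures somewhat.

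The consequences are lost precision, a mildly conservative test on the significance route, and a model left to discretion after the arms have been compared. A reader might infer a raised false-positive rate. The simulation shows the opposite for the significance route, and the effect of the discretionary route cannot be calculated because no rule is given.

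The power differences (78% against 83% at correlation 0.35, 80% against 97% at 0.7) come from a single-timepoint simplification with assumed correlations and effect. Gains for the time-by-group test would be smaller.

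**What to change.** In Statistical analysis (2.6):

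1. Delete the homogeneity-test trigger and the open route for variables deemed appropriate. Describe baseline by arm without p-values.
2. Name a short prognostic covariate set in advance, for example age and type of surgery (mastectomy or quadrantectomy), each with a covariate-by-time term.
3. Where groups are compared at T2 or T3 alone, adjust for the pre-randomisation score of that outcome instead of using an unadjusted ANOVA. Do not enter T0 or T1 as covariates in a model where they are response levels.
4. Put any other covariate in a labelled sensitivity analysis.
5. Reconcile sections 2.2.5 and 2.4.2 on when allocation occurs before treating T1 as a pre-randomisation value. T0 precedes allocation under either statement. If allocation precedes surgery, use the planned type of surgery.

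The cost is a rewritten paragraph and a few degrees of freedom. With two single-coefficient covariates, the error degrees of freedom for the interaction fall from 297 to (102 − 3 − 2) × 3 = 291. The sample size does not change. Age is already collected. Type of surgery is not in the article's list of collected variables, but scheduled mastectomy or quadrantectomy is an inclusion criterion, so I assume that it can be taken from the clinical record.

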### Study design

2.1

This study employs a prospective, longitudinal, single-blind RCT design with three primary assessment timepoints (T0, T1, T2) and a long-term follow-up assessment (T3), and experimental psychological intervention with random allocation of participants across three groups (Figure 1): (A) Control group (G1): Treatment as usual (TAU) receiving standard psychological support; (B) Active control group (G2): TAU plus psychoeducational intervention; (C) Experimental group (G3): TAU plus EMDR R-TEP protocol.

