#### Timeline and assessments

2.4.2

According to the flowchart of the study (Figure 1), participants will undergo six different steps.

*Baseline T0* (post-diagnosis, pre-hospitalization, pre-surgery): Participants will complete clinical interview and self-report psychological assessment battery.*Surgery:* participants will undergo breast surgery.*Follow-up T1* (within 1 week post-surgery): Participants will complete clinical interview and repeat self-report instruments to evaluate temporal changes.*Group assignment:* Following T1 assessment, participants will be randomly assigned to one of three groups, then follow their respective 8-week psychological intervention.*Follow-up T2* (psychological intervention completion, within 3 months post-surgery): All participants will complete the psychological assessment battery again to evaluate temporal changes.*Follow-up T3* (within 3 months post-psychological intervention): All participants will complete the psychological assessment battery again.

Participants who withdraw (dropout) from the study will not have their data considered in analyses. However, these individuals will continue receiving treatment benefits from their assigned condition. To ensure complete and optimal data analysis, questionnaires presenting missing data will be excluded from the study (Pozzar et al., 2020) – though participants will continue benefiting from assigned treatment.

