### Expected psychological outcomes

3.1

Based on the theoretical framework outlined in the Introduction, both the psychoeducational intervention (G2) and the EMDR R-TEP protocol (G3) are expected to demonstrate superior efficacy compared to TAU (G1), as both structured interventions specifically target core constructs relevant to this population. However, greater improvement is expected for individuals assigned to the EMDR R-TEP protocol at all timepoints, given its specific focus on trauma reprocessing through bilateral stimulation – directly addressing the traumatic underpinnings of psychological symptomatology in breast cancer patients following diagnosis and surgery. While the difference between the two structured interventions may be less pronounced at the earlier timepoint (T2), the superiority of EMDR R-TEP is hypothesized to be most evident at long-term follow-up (T3), in line with the trauma-focused literature and the mixed efficacy results for psychoeducational interventions.

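### The only test the plan sizes and requires is an omnibus group-by-time interaction over four visits, two before allocation; the R-TEP contrasts that carry the hypothesis are optional, untimed and unpowered

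*Protocol article*

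**What the plan says.** Section 2.2.4 sizes the trial on "repeated measures analysis of variance (ANOVA) with within-between interaction". The groups are entered as "treatment condition as between-group variable (TAU vs. TAU + psychoeducation vs. TAU+R-TEP") and the visits as "time as within-subject variable (T0, T1, T2, and T3; see dedicated section"). The effect size f "was set to 0.15 (small-to-medium effect size) and the correlation among repeated measures was set to 0.35". With alpha 0.05 and power 0.80, the result is 102 evaluable patients, about 34 per arm.

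Section 2.6 leaves the model class open (mixed model, repeated-measures ANOVA or Bayesian) but fixes one thing: "All models will test the interaction between time and intervention group". The same section names the three pairwise comparisons as post-hoc steps to be done where appropriate. Comparisons at single visits are optional. No visit is attached to the pairwise comparisons.

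On timing, section 2.4.2 states: "Following T1 assessment, participants will be randomly assigned to one of three groups". Section 2.2.5 instead places allocation within seven working days of the baseline assessment. The abstract describes T1 as preceding the psychological intervention, so no treatment effect is possible at T1 on either account.

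The hypothesis in section 1.8 is that R-TEP is superior both to TAU alone and to TAU with psychoeducation. On which visit matters most, section 2.1 speaks of "three primary assessment timepoints (T0, T1, T2) and a long-term follow-up assessment (T3"), whereas section 3.1 expects that "the superiority of EMDR R-TEP is hypothesized to be most evident at long-term follow-up (T3").

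**The concern.** There are two problems with relying on the interaction.

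First, it treats two pre-allocation visits as outcomes. Under section 2.4.2 the arms can differ at T0 and T1 only by chance, so the arm-by-visit comparison between them is null by design. The two scores would do more good as baseline covariates.

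Second, a 6-df interaction says only that the arm profiles are not parallel. It does not say which arm does better, at which visit, or against which comparator. A positive result is compatible with R-TEP equal to psychoeducation, or with psychoeducation alone working.

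The comparisons that would settle the hypothesis are conditional and have no visit attached, so which contrast at which visit counts as the answer could be decided after the data are seen. The 80% power, which section 3.3.2 presents as assurance of adequate power, belongs to the omnibus test. It says nothing about R-TEP versus psychoeducation.

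**Working it through.** **1. Reproduce the plan's figure.** Inputs from section 2.2.4: k = 3 arms, m = 4 visits, f = 0.15, rho = 0.35, alpha = 0.05, N = 102; sphericity assumed.

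- lambda = f² × N × m / (1 − rho) = 0.0225 × 102 × 4 / 0.65 = 14.12
- df1 = (3 − 1)(4 − 1) = 6; df2 = (102 − 3)(4 − 1) = 297
- Noncentral F power = 0.807. The smallest N reaching 80% is 101, or 102 with equal arms.

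The stated 102 is therefore the size for a 6-df test over all four visits.

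**2. Where the 6 df go.** They split into three orthogonal 2-df parts: T1 minus T0 by arm, T3 minus T2 by arm, and the post mean (T2, T3) minus the pre mean (T0, T1) by arm. The first is null because allocation follows T1. If the effect is equal at T2 and T3, the second is null too and all of lambda lies in the third. There, with 2 and 99 df, power is 0.92 instead of 0.81.

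**3. Direction.** Assume no arm difference at T0/T1 and a constant effect at T2 and T3. Then f² = (mean squared deviation of the arm effects) / 4.

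- R-TEP = psychoeducation, both better than TAU by d: f² = d²/18, so d = 0.15 × √18 = 0.636 SD. lambda is again 14.12 and power 0.807, although the hypothesis against psychoeducation is false.
- Only psychoeducation works: same d, same 0.807.

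**4. Power of the contrasts the hypothesis needs.** Assume compound symmetry with rho = 0.35, 34 per arm and two-sided 0.05 per contrast, with adjustment for T0 and T1.

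- Residual variance of the T2/T3 average: 0.675 − 0.35²/0.675 = 0.494, where 0.675 = (1 + 0.35)/2. Standard error of a difference = √(2 × 0.494/34) = 0.170.
- Residual variance at T3: 1 − 0.35²/0.675 = 0.819. Standard error = √(2 × 0.819/34) = 0.219.
- Psychoeducation midway (0, d/2, d): f² = d²/24, so d = 0.15 × √24 = 0.735 and d/2 = 0.367.
- Only R-TEP works (0, 0, d): d = 0.636.

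| Sustained pattern (assumed) | Contrast | T2/T3 average | T3 |
|---|---|---|---|
| Psychoeducation midway | R-TEP vs TAU | 0.735/0.170: power 0.99 | 0.735/0.219: power 0.91 |
| Psychoeducation midway | R-TEP vs psychoeducation | 0.367/0.170: power 0.57 | 0.367/0.219: power 0.38 |
| Only R-TEP works | either contrast | 0.636/0.170: power 0.96 | 0.636/0.219: power 0.82 |

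For 80% power on R-TEP versus psychoeducation in the midway pattern, about 177 evaluable patients are needed for the average and about 288 for T3.

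The baseline scores do help. A plain change contrast (post mean minus pre mean, variance 0.65) has 0.46 for R-TEP versus psychoeducation in that pattern, against 0.57 with covariate adjustment.

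**5. Other effect patterns, scaled to f = 0.15.** These are 2-df baseline-adjusted arm tests, and the interaction stays at 0.807 throughout.

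- Effect at T3 only, psychoeducation midway (f² = d²/32, d = 0.849): T3 test 0.94; T2/T3 average 0.585. The R-TEP versus psychoeducation contrast at T3 has 0.48.
- Effect halves from T2 to T3: T3 test 0.41.
- Effect at T2 only: T3 test 0.05, that is, no power above alpha.

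**The case against.** Four points can be made for the plan.

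- **Omnibus test then pairwise comparisons is a standard route.** Section 2.6 names R-TEP versus TAU and R-TEP versus psychoeducation, provides for effect sizes, and allows a false discovery rate correction on the primary outcomes. This stands in part. A reader might infer that the plan never tests its hypothesis; the text does not support that. What remains is that these comparisons are conditional, have no visit attached and are not sized.
- **The interaction is robust to the shape of the effect.** It keeps about 0.81 in every pattern scaled to f = 0.15, while a targeted test can fall to 0.585, 0.41 or alpha if the wrong time is chosen. This stands. A reader might infer that the interaction always wastes power, or that replacing it always gains power; step 5 shows otherwise. High powers such as 0.975 for the T2/T3 average with a sustained effect belong to 2-df arm tests, which are as non-directional as the interaction.
- **The article labels no primary test and does not mention 6 df.** True; both are inferred. But the stated 102 reproduces only as that test, and section 2.6 requires it of every model. Finer detail may sit in an analysis plan not shown; the point rests on what the article itself fixes.
- **The T2/T3 discrepancy is mild.** Section 2.1 describes a visit schedule. Section 3.1 is a Discussion expectation that also predicts an R-TEP advantage at all timepoints. This stands: a reader might take T3 as the designated primary visit, but the document designates none.

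**Conclusion.** The concern holds in a limited form. The one test that is sized and required is a 6-df omnibus interaction (power 0.807 at 102). It spends 2 df on a pre-allocation change that is null by design, and it cannot by itself show that R-TEP beats both comparators, since it is as likely to be positive when R-TEP only equals psychoeducation. Under the plan's own f and rho, the harder half of the hypothesis, R-TEP versus psychoeducation, has power between 0.38 and 0.96 across the sustained patterns and times in step 4. The 80% figure is therefore no assurance on it.

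These figures rest on compound symmetry, 102 evaluable patients, no arm difference before treatment, a sustained effect, and an assumed position for psychoeducation that the protocol does not quantify. They apply no correction for multiple testing; at 0.025 per contrast, the 0.57 becomes 0.46. The change is worth making, but the trial is not invalid as designed.

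**What to change.** Make the primary analysis of each primary outcome a linear mixed model of the T2 and T3 scores with arm, visit and arm-by-visit, adjusted for the T0 and T1 scores of the same scale. Prespecify R-TEP minus TAU and R-TEP minus psychoeducation as the primary contrasts, each with a 95% confidence interval. Name the post-treatment time (T2, T3 or their average) before unblinded data are seen, and bring sections 2.1 and 3.1 into line with that choice. Reconcile sections 2.2.5 and 2.4.2 on when allocation occurs. Keep the four-visit interaction as supportive. In section 2.2.4, state the power of the two contrasts, with the assumed effect pattern, instead of relying on the interaction's 80%.

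The change needs no new data or visits. It has two costs. The trial commits to one post-treatment summary and loses the interaction's protection against an unexpected pattern. And the declared power for R-TEP versus psychoeducation will look less favourable: unless the sample is enlarged (about 177 evaluable for the average or 288 for T3 in the midway pattern), that limit should be stated openly.

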Additionally, between-group comparisons at each timepoint may be performed using appropriate statistical tests depending on data distribution (e.g., one-way ANOVA or Kruskal-Wallis). If appropriate, post-hoc pairwise comparisons (R-TEP vs. TAU, R-TEP vs. psychoeducation, psychoeducation vs. TAU) will be conducted to identify specific group differences. Within-group comparisons across timepoints (e.g., T0 vs. T1, T1 vs. T2) may also be examined to evaluate change trajectories within each condition. Effect sizes (e.g., Cohen’s d for pairwise comparisons, partial η^2^ for omnibus tests) will be reported to facilitate clinical interpretation (Cohen, 1988). If necessary, to control for Type I error inflation due to multiple testing, the False Discovery Rate (FDR) correction procedure will be applied to the primary outcomes (Benjamini and Hochberg, 1995; Storey, 2002). Secondary outcomes will be analyzed as exploratory. Moreover, if Bayesian approaches are employed, Bayes Factors will be reported to quantify evidence strength for both alternative and null hypotheses (Greenland and Poole, 1994; Kass and Raftery, 1995; Lavine and Schervish, 1999; Held and Ott, 2018).

At individual level, parameters identifying significant changes both statistically (e.g., Reliable Change Index) and/or clinically (e.g., Minimal Clinically Important Difference) could be calculated (Maassen, 2000, 2001; Turner et al., 2010). Additionally, when available, individual scores will be compared with normative scores (expressed in Z or T points) to evaluate symptom severity relative to reference population (Howell, 2013; Tabachnick and Fidell, 2019).

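### The only tests named for the optional per-visit arm comparisons ignore each patient's own pre-treatment score and give up about 5 to 8 points of power

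*Protocol article*

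**What the plan says.** The sample size (section 2.2.4) is for a "repeated measures analysis of variance (ANOVA) with within-between interaction", with three arms and four visits. The effect size f "was set to 0.15 (small-to-medium effect size"), alpha "was set to 0.05 (two-sided"), power "was set at 0.80", and "the correlation among repeated measures was set to 0.35". The result is 102 analysable patients, about 34 per arm.

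Section 2.6 makes a repeated-measures model the group-level analysis, with the time-by-group interaction as its test. It then adds, as an option, that "between-group comparisons at each timepoint may be performed using appropriate statistical tests depending on data distribution (e.g., one-way ANOVA or Kruskal-Wallis"). The next sentence allows pairwise arm comparisons where appropriate. Covariates may enter the models if judged appropriate or if the arms differ. The examples given are age, comorbidity and social support; a patient's own earlier score on the outcome is not among them.

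All scales are completed at T0, T1, T2 and T3. Section 2.4.2 places allocation after the second of these: "Following T1 assessment, participants will be randomly assigned to one of three groups". Section 2.2.5 instead ties allocation to a window of seven working days after baseline. Section 3.1 states a visit-specific expectation: "the superiority of EMDR R-TEP is hypothesized to be most evident at long-term follow-up (T3").

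**The concern.** By the time therapy starts, every patient has two scores on PDI-R and two on PTSQ. The sample size assumes that these scores correlate with the later ones. One-way ANOVA and Kruskal-Wallis treat a T2 or T3 score as if nothing were known about the patient beforehand, and Kruskal-Wallis cannot take a covariate at all.

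Two things follow. The per-visit comparisons of R-TEP with TAU and with psychoeducation have less power than the collected data allow. A chance difference between arms before treatment also passes uncorrected into the T2 and T3 comparison. At a correlation of 0.35, a chance difference of 0.3 SD at T1 moves the expected raw contrast by 0.35 × 0.3 ≈ 0.1 SD. Because section 3.1 expects the clearest advantage at one particular visit, readers will look at these comparisons even though they are supplementary.

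Read literally, the wording also covers T0 and T1. No therapy has been given at those visits, so a test between arms there answers no efficacy question.

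**Working it through.** **Inputs from section 2.2.4:** f = 0.15 for the interaction, correlation 0.35, two-sided alpha 0.05, N = 102 (34 per arm), three arms, four visits. **Assumptions:** the correlation is the same for every pair of visits, and the effect sizes at a single visit are derived in step 2.

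**1. The plan's own figure.** Interaction non-centrality = f² × N × 4 / (1 − 0.35) = 0.0225 × 102 × 4 / 0.65 = 14.12, with 6 and 297 degrees of freedom. Power is 80.7%. The smallest N with equal arms that reaches 80% is 102, so the stated sample size reproduces.

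**2. Effect at one visit implied by f = 0.15.**
- Equal effect at T2 and T3, none before: the visit indicator has variance 1/4, so the per-visit f = 0.15 / √(1/4) = 0.30.
- Effect at T3 only: the variance is 3/16, so the per-visit f = 0.15 / √(3/16) = 0.346.
- An f of about 0.30 corresponds to R-TEP better by 0.64 SD with psychoeducation equal to TAU (0.64 × √(2/9) = 0.302), or to R-TEP better by 0.735 SD with psychoeducation midway (0.735 / √6 = 0.300).

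**3. Variance explained by the earlier scores.**
- One score: R² = 0.35² = 0.1225.
- T0 and T1: R² = 2 × 0.35² / (1 + 0.35) = 0.1815, leaving a residual variance factor of 0.82.

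**4. Power at one visit.** For the three-arm test, use the noncentral F with 2 and 99 degrees of freedom unadjusted, or 98 or 97 adjusted, and non-centrality N f² / (1 − R²). For the pairwise test, use the noncentral t with pooled error.

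| Comparison | Unadjusted | One earlier score | T0 and T1 |
|---|---|---|---|
| Three-arm, f = 0.30 (T2 and T3) | 76.6% | 82.1% | 84.8% |
| Three-arm, f = 0.346 (T3 only) | 88.0% | 91.9% | 93.6% |
| Pairwise, 0.64 SD | 74.3% | about 79% | about 82% |

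A simulation of 10,000 trials at f = 0.30 gave 76.6% for ANOVA, 74.0% for Kruskal-Wallis, 81.9% for ANCOVA on one score and 84.4% for ANCOVA on both. With no effect, simulated rejection rates were 5.2% (ANOVA), 5.0% (Kruskal-Wallis) and 4.9% (ANCOVA on both), so all three tests hold their level.

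**5. Would any mixed model give the same gain?** No. With complete data, T0 and T1 entered as outcomes and a free mean for every arm at every visit, the estimated arm contrast at T3 equals the raw difference in means. Its variance is 2/34 = 0.0588 in SD² units. If the T0 and T1 means are constrained equal across arms, the variance falls to 0.0481, a ratio of 0.82, which matches step 3.

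**The case against.** The strongest reply is that little is fixed here. The comparisons are additional, may or may not be done, and the two tests are only examples, so an adjusted comparison would already fit the wording. The main analysis is the repeated-measures interaction, which uses all four visits and is the test the trial was sized for. Covariates are allowed in open-ended terms, and a condensed article may leave such detail to an analysis plan.

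Much of this stands, and it limits the point. A reader might infer that the trial's powered analysis is short of power. It is not: that test reproduces at 80.7%. A reader might infer an inflated false-positive rate. It is not inflated. A reader might also infer that these tests are the only route to the T3 hypothesis. The document does not say so: greater improvement over time is also a time-by-group question, and the pairwise comparisons could follow the interaction model.

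What remains does not rest on silence. Both examples the article gives are unadjusted, one cannot be adjusted, and neither the examples nor the covariate rule mentions the outcome's own earlier score.

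**Conclusion.** The point holds as a modest gain in efficiency for optional comparisons. At 34 per arm and a constant correlation of 0.35, with unadjusted power of about 74% to 77%, the named tests give up about 7 to 8 points against ANCOVA on T0 and T1. The loss is about 5 points if only one earlier score is used, and about 6 points if the effect is at T3 only. Kruskal-Wallis on normal data loses roughly 2 to 3 points more.

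The size depends on the assumed correlation. At 0.5, the pairwise figures at 0.64 SD become 74% unadjusted and 89% adjusted for both scores. It also depends on T1 preceding allocation, on which sections 2.2.5 and 2.4.2 disagree. The per-visit effect sizes are assumptions matched to f = 0.15; the article does not state them.

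**What to change.** In section 2.6, replace the two example tests. State that the between-arm and pairwise comparisons at T2 and T3 will be made by ANCOVA adjusted for the same scale's T0 and T1 scores. The alternative is a mixed model of T2 and T3 with those scores as covariates, or a mixed model of all visits with pre-treatment means constrained equal across arms. An unconstrained mixed model with T0 and T1 as outcomes should not be offered as equivalent, because it does not give the gain.

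Reconcile sections 2.2.5 and 2.4.2 on when allocation takes place. If it precedes T1, adjust for T0 only. If residuals are clearly non-normal, use rank-based ANCOVA or bootstrap standard errors in place of Kruskal-Wallis. Report T0 and T1 by arm descriptively.

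The cost is one sentence of text and one or two model degrees of freedom, which the adjusted power figures already include. No further patients, visits or data are needed.
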